### Description of the “APA” arm

In addition to PA recommendations, participants randomized to this arm will receive PA sessions via videoconference for 6 months. The sessions will be based on the personalized PA assessment and will last between 45 min (at the beginning of the program) and 1 h, 1 to 3 times a week, supervised or on their own. Participants will benefit from this program free of charge (Table 1).

**Table 1 Tab1:** Duration and type of PA proposed

Physical activity	Month #1	Month #2	Month #3	Month #4	Month #5	Month #6
Pilates/stretching/yoga Intensity: light to moderate *Sessions with APA teacher*	45 min	45 min	60 min	60 min	60 min	60 min
Cardio fitness Intensity: light *Sessions with APA teacher*			60 min	60 min		
Cardio Intensity: light to moderate *Sessions with APA teacher*					60 min	60 min
Pilates/stretching/yoga + cardio fitness Intensity: light to moderate *Autonomous sessions*				Duration decided by participants		
Total duration of PA from the study	45 min	45 min	120 min	> 120 min	> 120 min	> 120 min

### Initial contact

After the assessment by the APA teacher and before the start of the program, the APA teacher will explain to the participants how the videoconference platform works. He/she will then present the personalized APA program to them.

### Assessment of PA level at inclusion

The PA tests carried out at inclusion will allow the evaluation of the level (beginner, intermediate, expert) of the participants in aerobic activity, mobility, balance, and flexibility.

### APA program

#### Program structure

The 6-month APA program will be supervised via the videoconferencing platform and/or performed independently based on a personalized written program that is updated weekly or bi-weekly by the APA teacher. The program will be based on structured sessions alternating two types of PA: cardio fitness sessions and stretching/yoga/Pilates sessions (to be practiced following the teacher’s oral or written instructions). Each session will last from 45 min to 1 h and will be of low to moderate intensity depending on the level of physical condition at the start. A maximum of 6 participants will be able to attend a session.

The sessions will be structured, adapted, and progressive. During the sessions, the exercises will be adapted according to the means and materials available to the patients at home or in their immediate environment.

#### Structured sessions

Each session will include the following:A warm-up periodStretching, yoga, Pilates, or endurance during the cardio fitness sessions (light to moderate)A recovery period consisting of stretching and relaxation

The duration and intensity of the sessions will be modified according to the physical evaluation and the patients’ declarations at the beginning of each session. In case of intense fatigue and pain, the sessions will be adapted.

The duration and the intensity of the sessions will also evolve according to the capacities of the patients evaluated in a declarative way at the end of each realized session: pain, fatigue, and quality of life.

#### Course of the sessions in autonomy

The patients will be progressively led to practice in an autonomous way (i.e., without supervision) but following an adapted, personalized, and structured program. These PA sessions can be declared afterwards to the PA teacher, specifying the duration of the activity and the exercises actually performed.

### End of the intervention

At the end of the 6-month intervention, participants will keep all records of their written program in order to keep ideas of exercises and to encourage them to continue regular unsupervised exercise on their own. If a contraindication (e.g., injury, not planned but necessary surgery) to PA occurs during the intervention, the participant will be asked to interrupt the program.

### Description of the “education” arm

In addition to the recommendations in terms of PA, participants will benefit from 6 months of education sessions which will include 12 sessions (1-h duration, twice a month) scheduled according to the availability of the participants and by videoconference. Two types of sessions will be proposed: sessions “between participants only” (with the PI), to discuss of general problems linked to endometriosis and tips to manage it, and sessions with an endometriosis specialist (gynecologic surgeon, pain specialist, micronutritionist, physiotherapist). These sessions will help them to better understand endometriosis symptoms and its management. A final individual session will be held at the end of the intervention and will allow for an informal educational assessment.

### Description of the CRESCENDO program: “APA + education” arm

In addition to the PA recommendations, participants in the “APA + education” arm will benefit from both the APA arm and education arm programs.

### Description of the waitlist control group

Participants randomized to this arm will receive written PA recommendations (booklet) and a video of movements to perform, without further intervention. These individuals will receive the PA and education program (3–6 months) at the end of their initial program.

### Criteria for discontinuing or modifying allocated interventions {11b}

If two participants (A and B) live together and are not randomly allocated to the same arm, because of the potential contamination, the second person (B) to be randomized will be allocated to the first participant (A)’s arm. There are no other criteria for discontinuing or modifying allocated interventions. Participants may withdraw voluntary from trial participation at any point. They can give none or any reason to do so. They will be informed that withdrawal from the study has no negative consequences or disadvantages on their care. The PI might also terminate participation if contraindications or severe adverse events arise during the intervention.

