### Who will take informed consent? {26a}

Informed consent will be managed by the principal investigator (PI). Patients will be informed by their endometriosis specialists in one of the French health centers partners to this program (i.e., La Croix Rousse Hospital Lyon, Strasbourg Hospital, Grenoble Hospital, Nimes Hospital, Mulhouse Hospital) of the existence of the program, and the latter will give them a flyer of the program with the PI’s email. Once the email is received, the PI will send the consent form containing written information about study (e.g., aim, duration, data collections during and after the program, randomization process) and will invite the potential participants to discuss the program via a one-to-one scheduled videoconference (will also allow to ensure the technology and Internet access). This first videoconference contact will last 30 min. This meeting will allow to extensively present the study and answer potential participant’s questions. Then, participants will be asked to send written informed consent when they want (within a few hours, days, or weeks) to ensure that consent is given without any pressure and to leave time to read again the written information.

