## Assignment of interventions: allocation

### Sequence generation {16a}

Participants will be randomized to one of the four arms using complete randomization which consist of uniformly distributing them. This procedure is performed using an R script. We opted for this procedure to avoid selection bias as this is the only procedure that does not permit to guess the assignment (Supplementary Material). Moreover, it minimizes various bias and various methods allows to correct the bias provoked by unbalanced in arms [56].

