### Concealment mechanism {16b}

Each participant will be entered in the database to be allocated only once the consent form and the baseline online questionnaire are completed and sent to the principal investigator. Thus, each participant will be included chronologically, the date and hour of the last document sent in the principal investigator’s mailbox being the references. The principal investigator is the only one to know when the document was received. Allocation concealment will be ensured as R script will not release the randomization code until the patient has been included into the trial.

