### Implementation {16c}

Randomization will be implemented by the principal investigator. Participants will receive an email to inform them about their allocation.

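### A cohabitant who joins after the first participant was allocated has an arm known in advance, and the investigator who enrols also runs the allocation

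*Protocol article*

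**What the plan says.** **Cohabitants.** The section on criteria for discontinuing or modifying allocated interventions {11b} sets a rule against contamination. The trigger is "If two participants (A and B) live together and are not randomly allocated to the same arm". The consequence is that "the second person (B) to be randomized will be allocated to the first participant", that is, to A's arm.

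**Disclosure.** Under Implementation {16c}, "Participants will receive an email to inform them about their allocation". Under Who will be blinded {17a}, neither researchers nor participants are blinded.

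**Claims about concealment.** Sequence generation {16a} justifies complete randomisation on the ground that "this is the only procedure that does not permit to guess the assignment". Concealment mechanism {16b} says: "Allocation concealment will be ensured as R script will not release the randomization code until the patient has been included into the trial". Neither section makes an exception for cohabitants. The same {16b} section allocates a participant only after both the consent form and the baseline questionnaire have been sent in, in order of the date and hour of the last document.

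**Who does what.** Consent, including the one-to-one videoconference before it, lies with the principal investigator (Who will take informed consent? {26a}). On the order of entry, "The principal investigator is the only one to know when the document was received" {16b}. On allocation, "Randomization will be implemented by the principal investigator" {16c}. The section on the coordinating centre and steering committee {5d} gives the first videoconference, randomisation and collection of consent forms to the principal investigator and a post-doctoral fellow together.

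**The concern.** Two features weaken the protection that randomisation is meant to give.

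First, the cohabitation rule replaces B's draw with an arm that is already fixed. If that arm is known when B decides whether to take part, B may join because A received the full programme, or stay out because A is on the waitlist. B may also answer the baseline questionnaire knowing the arm.

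Second, the stated safeguard is that the script withholds the code until inclusion. The person who establishes inclusion also runs the script, so the safeguard does not place a second party between enrolment and allocation.

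Both matter more here than in a blinded trial. The primary outcome is self-reported quality of life, the design is open label and the comparator is a waitlist, so concealed random allocation is the main defence against selection bias. The section on additional analyses {20b} also relies on the randomisation procedure, with the sample size, to prevent differences between arms.

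**Working it through.** The protocol gives no figure for cohabiting participants, so there is none to reproduce. The inputs from the document are the 1:1:1:1 ratio (Trial design {8}) and 200 participants (Sample size {14}). The number of pairs and the intra-household correlation below are assumptions.

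**Step 1. B's final arm.**
- If A and B draw different arms, the rule moves B to A's arm.
- If they draw the same arm, B is already there.
- Hence B's final arm equals A's in every case.

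**Step 2. How often a draw for B is overridden.** With four equally likely arms, P(same arm) = 4 × (1/4)² = 0.25, so P(overridden) = 1 − 0.25 = 0.75.

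**Step 3. When the arm is foreknown.**
- *A allocated and told before B consents:* the investigator knows A's arm from running the script, A knows it from the email, and B lives with A. The probability of naming B's arm correctly rises from 0.25 to 1.00. B's consent and baseline questionnaire both come after that knowledge is available.
- *A and B both complete consent and baseline before either is allocated:* B inherits A's random draw. In effect the household is randomised once, and nobody has foreknowledge.

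The text of {11b} covers both orders and does not distinguish them.

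**Step 4. Number affected** (assumed pairs p among 200; at most one B per pair):

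| Pairs p | Bs as share of 200 (p/200) | Expected overridden draws (0.75p) |
|---|---|---|
| 1 | 0.5% | 0.75 |
| 5 | 2.5% | 3.75 |
| 10 | 5% | 7.5 |
| 20 | 10% | 15 |

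If 2–5% of participants live with another participant, that is 4–10 people, or 2–5 pairs. Only pairs in which B joins later carry foreknowledge, so these counts are upper limits for that problem.

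**Step 5. Cost in precision of randomising households.** Design effect = 1 + (Σmᵢ²/N − 1) × ICC, where mᵢ is household size. With p pairs, Σmᵢ² = (200 − 2p) + 4p = 200 + 2p, so the design effect is 1 + (p/100) × ICC.
- p = 1, ICC = 0.1: 1 + 0.01 × 0.1 = 1.001.
- p = 20, ICC = 0.5: 1 + 0.20 × 0.5 = 1.10.
- p = 5, ICC = 0.3: 1 + 0.05 × 0.3 = 1.015.

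**Step 6. Separation of roles.** No arithmetic applies. Set side by side, {26a}, {16b} and {16c} put consent, sole knowledge of the order of receipt, and allocation with the same investigator. {5d} adds a post-doctoral fellow but gives that person the same combination of tasks. None of these sections assigns allocation to anyone outside enrolment.

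**The case against.** The cohabitation rule has a sound reason, contamination, and for two people who enrol together it amounts to household randomisation. The number of pairs is unknown. Both members would need diagnosed endometriosis and would have to meet every other criterion, so pairs will be rare and any effect on balance or power minor. All of this stands, and it limits the point to later-joining cohabitants.

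On roles, {16b} already requires consent and baseline before allocation, and emailed documents leave a time record. Complete randomisation makes the next arm unpredictable from earlier ones. This also stands: for participants who do not live with another participant, nothing in the text shows that the arm can be guessed.

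Three stronger readings are tempting but not supported:
- *A reader might infer that the script can be rerun, or the order changed, without trace.* The script is in supplementary material that is not shown. Whether it fixes a seed or logs its runs is unknown.
- *A reader might infer that concealment fails for all 200.* The text shows an unseparated role, which is an opportunity. It does not show foreknowledge or misuse.
- *A reader might infer that B is wrongly analysed as randomised, with clustering ignored.* Analysis sets and standard errors belong to the statistical analysis plan, which exists separately and is not shown.

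What the objection does not remove is the conflict between {11b} and the unqualified claims in {16a} and {16b}. Nor does it supply the missing separation between enrolling and allocating. An analysis plan could decide how B is handled, but it could not undo B's foreknowledge or change who runs the script.

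**Conclusion.** The point holds in a limited form. For a cohabitant who joins after the first participant was allocated and told, the arm is determined (1.00 rather than 0.25) and can be known before consent and baseline. The claims in {16a} and {16b} are therefore wrong for that person. On an assumed 2–5 pairs this concerns at most 2–5 of 200 participants (1–2.5%), with little effect on power or balance. It rests on B learning A's arm, which is likely in a shared home and an open-label trial but is not stated.

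Separately, the protocol's safeguard does not separate enrolment from allocation. The consequence cannot be quantified from the document. It is a weakness of procedure that is cheap to remove, not a demonstrated bias.

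**What to change.** 1. Ask about cohabiting participants at the first videoconference, which is already planned. When both wish to join, randomise the pair once as a household, before either allocation is released.
2. Let a cohabitant who appears after the first was allocated follow that arm, as the rule now provides, but leave every such person out of the randomised comparison. This should include those whose own draw happened to match, because the foreknowledge is the same.
3. State this exception in {16a} and {16b}, and check that the analysis plan agrees on the analysis set and on allowing for correlation within pairs.
4. Have an existing team member who takes no part in enrolment, for example a trial biostatistician, hold and run the script. That person returns the allocation on receipt of the time-stamped consent and baseline forms and keeps a log.

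The cost is protocol wording and a hand-over between existing staff, a short delay in allocation, and the loss of a few late cohabitants from the primary set. One drawback should be weighed: under {5d} the biostatisticians also verify and analyse the data, so the person holding the sequence would be an analyst as well. If that is unwelcome, another member outside enrolment and analysis could take the task.

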### Strategies to improve adherence to interventions {11c}

In addition to the follow-up by the APA teacher for the two arms proposing APA, a telephone or email follow-up will be carried to ensure the good implementation of the program (at 1, 2, 4, and 5 months). Participants will be stimulated and encouraged to remain physically active on a daily basis. Patients will be able to contact PI at any time, by email or by phone. The adherence will be monitored by the attendance at the APA sessions and at the education sessions.

APA teachers will be also given with a notebook about the teaching strategies to motivate participants and maintain their motivation. These strategies are from the self-determination theory [36–38], a theory often used in promotion of PA in several context including health context. This could also limit the “APA teacher” effect which are differences or changes that can be due to the teacher who led the session and not to the intervention.

### Relevant concomitant care permitted or prohibited during the trial {11d}

Any treatment or change in treatment with direct influence on trial outcomes is permitted during the trial, because in endometriosis context, it could take time to find the adequate treatment, and it could be necessary to test and change this treatment every 3 or 4 months.

### Provisions for post-trial care {30}

Participants in the waitlist control group will benefit from APA session after the end of the main study (i.e., 6 months after their inclusion). Participants in APA arm will benefit from the minutes of the education sessions.

## Outcomes {12}

### Primary outcome measure

The aim of the study is will be to investigate potential change in QoL between baseline, middle (3 months) and end of the study (6 months), and 3- and 6-month follow-up. Greater improvements are expected in the APA + education arm compared to the waitlist control group.

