**Methods:**

This multicentric randomized-controlled trial will propose to 200 patients with endometriosis to be part of a trial which includes a 6-month program with 45 min to more than 120 min a week of adapted physical activity and/or 12 sessions of endometriosis-based education program. Effects of the program will be compared to a control group in which patients will be placed on a waiting list. All participants will be followed up 3 and 6 months after the intervention. None of the participants will be blind to the allocated trial arm. The primary outcome measure will be quality of life. Secondary outcomes will include endometriosis-related perceived pain, fatigue, physical activity, and also self-image, stereotypes, motivational variables, perceived support, kinesiophobia, basic psychological need related to physical activity, and physical activity barriers. General linear models and multilevel models will be performed. Predictor, moderator, and mediator variables will be investigated.

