### Trial design {8}

The study will be a multicentric randomized-controlled superiority trial which will include four arms (i.e., “APA,” “education,” “APA + education,” and “waitlist control group”) and will test the effect of a 6-month program on QoL in patients with endometriosis. The efficacy of the program in intervention groups will be compared to a control group (i.e., waitlist group control) which will benefit from APA and education sessions at the end of the 6 months program. Randomization will be balanced with a 1:1:1:1 ratio for patients’ allocation to the three intervention groups and the waitlist control group. Identifying potential moderators and mediators of treatment outcome will also be a component of this trial.

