## Data collection and management

### Plans for assessment and collection of outcomes {18a}

Variables will be assessed (1) online via self-report measures and (2) via the questionnaire proposed by the APA teacher at the beginning and at the end of the APA sessions. Primary outcomes will be assessed at baseline, 3 months, 6 months (end of the study), and at 3 and 6 months’ follow-up for all arms. Secondary outcomes will be assessed at baseline, 6 months (end of the study), and 6 months’ follow-up. Sociodemographic variables will be assessed at baseline only.

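### The waitlist arm starts the programme at about month 6, yet the primary outcome includes both later follow-ups without limiting the waitlist contrast to the visits before crossover

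*Protocol article*

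**What the plan says.** In the protocol article, Primary outcome measure sets the aim as investigating "potential change in QoL between baseline, middle (3 months) and end of the study (6 months), and 3- and 6-month follow-up". The next sentence gives the contrast without naming a visit: "Greater improvements are expected in the APA + education arm compared to the waitlist control group". Plans for assessment and collection of outcomes {18a} collects primary outcomes "at baseline, 3 months, 6 months (end of the study), and at 3 and 6 months’ follow-up for all arms". The abstract's Methods paragraph counts follow-up from the end of the intervention: "All participants will be followed up 3 and 6 months after the intervention".

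Trial design {8} describes a waitlist control group "which will benefit from APA and education sessions at the end of the 6 months program". Description of the waitlist control group adds: "These individuals will receive the PA and education program (3–6 months) at the end of their initial program". Explanation for the choice of comparators {6b} and Provisions for post-trial care {30} also place this start 6 months in. The post-trial care section names only APA for the waitlist, and adds: "Participants in APA arm will benefit from the minutes of the education sessions". It gives no date for those minutes.

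Statistical methods {20a} plans general linear and multilevel models comparing group means with repeated measures, and refers to a separate analysis plan.

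**The concern.** The primary outcome runs past the point at which the control group begins the intervention. At both follow-ups the waitlist arm is in the programme or has had it, so a difference from APA + education there no longer measures programme against no programme. It compares an earlier start with a later one.

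If all visits enter one comparison, two different quantities are combined. A programme that works, and works equally well when the waitlist receives it, would show a gap that widens to month 6 and then closes. A reader could take this for an effect that wears off. A claim of lasting benefit over an untreated control would have no support, although the protocol's introduction presents 6-month follow-up as an advance on earlier trials. Pain, fatigue and physical activity are measured at the same visits and share the problem.

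**Working it through.** The protocol gives no effect size by visit, so there is no figure of its own to reproduce. The check is first one of timing, then an illustration under stated assumptions.

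**Timing.** The programme lasts 6 months, and follow-up comes 3 and 6 months after it. The post-baseline visits are therefore months 3, 6, 6 + 3 = 9 and 6 + 6 = 12. The waitlist programme starts at about month 6 and lasts 3 to 6 months, so it ends between months 9 and 12.

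| Visit | Waitlist status |
|---|---|
| Month 3 | before programme |
| Month 6 | before programme |
| Month 9 | in the programme or just finished |
| Month 12 | programme finished or finishing |

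Two of the four post-baseline visits have a programme-free control and two do not.

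**Assumptions (not in the protocol).** Let D be the full effect. The programme gives 0.5D after 3 months and D after 6 months, and the effect is then maintained. Three courses are considered for the waitlist after month 6: no programme; the same response as the active arm; or a gain of only 0.5D, reached by month 9 and held.

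Differences between APA + education and waitlist, in units of D, at months 0, 3, 6, 9 and 12:

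- No crossover: 0, 0.5, 1, 1, 1
- Same response: 0, 0.5, 1, 0.5, 0
- Half response: 0, 0.5, 1, 0.5, 0.5

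**Time-averaged effect (mean of the four post-baseline differences).**

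- No crossover: (0.5 + 1 + 1 + 1)/4 = 0.875
- Same response: (0.5 + 1 + 0.5 + 0)/4 = 0.5; loss 1 − 0.5/0.875 = 43%
- Half response: (0.5 + 1 + 0.5 + 0.5)/4 = 0.625; loss 1 − 0.625/0.875 = 29%

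**Group-by-time effect.** With two arms and equal correlation between visits (assumed), the signal is the sum of squares (SS) of the five differences about their own mean. Effect size is proportional to its square root.

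- No crossover, mean 0.7: SS = 0.49 + 0.04 + 3 × 0.09 = 0.80
- Same response, mean 0.4: SS = 0.16 + 0.01 + 0.36 + 0.01 + 0.16 = 0.70; loss 1 − √(0.70/0.80) = about 6%
- Half response, mean 0.5: SS = 0.25 + 0 + 0.25 + 0 + 0 = 0.50; loss 1 − √(0.50/0.80) = about 21%

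The ordering reverses between the two tests. A full waitlist response costs the time average most, but it costs the interaction test least, because the closing gap itself counts as interaction. In that case the test may well reach significance, but the pattern behind it is not a fading treatment effect.

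**The case against.** The strongest reply is that the protocol never says outright that the waitlist is the comparator at follow-up. The sentence giving the contrast names no visit, the trial tests a 6-month programme, and several sections call month 6 the end of the study. A month-6 primary contrast, with later visits for maintenance, is a possible reading, and the separate analysis plan, not seen here, may state it. This stands to the extent that the comparator role at follow-up is an inference. But the primary outcome itself lists the follow-ups, they are collected "follow-up for all arms", and the caption of the schedule figure calls the last visit the endline assessment. Nothing in the protocol sets the restriction.

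Two other readings of the timing do not help. Post-trial care refers to the end of the main study, but the same sentence defines that as 6 months after inclusion. If waitlist follow-up were counted from the waitlist's own programme, the arm would still have been treated, and its visits would no longer be concurrent with those of the other arms.

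A reader might infer that the primary test is biased toward no effect by 43%. The documents do not support that: they specify no single primary test, and 43% belongs to a time average under one assumed pattern. A reader might also infer that the education minutes contaminate the APA versus APA + education comparison at follow-up. That depends on a date the protocol does not give, and written minutes are not the 12 live sessions.

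**Conclusion.** The concern holds in this form: two of the four post-baseline visits in the primary outcome fall after the waitlist starts the programme, and the protocol does not limit the waitlist contrast to the visits before that. The timing rests on the document alone. The size depends on the analysis chosen and on the assumed response: about 43% or 29% off a time-averaged effect, and about 6% or 21% off a group-by-time effect size, for a full or half waitlist response respectively.

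The randomised contrasts with the waitlist at months 3 and 6 are unaffected. Follow-up comparisons among the three active arms do not involve the waitlist, so it would go too far to say that no controlled comparison exists after month 6. What is lost is the comparison with people who have not had the programme. Untreated here means without the programme, since the waitlist receives a booklet, a video and usual care from the start.

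**What to change.** - Name one primary contrast: APA + education minus waitlist in EHP score at 6 months, before crossover, with month 3 supportive. A visit-specific estimate from a model fitted to all visits would serve.
- Do not use the waitlist as an untreated control at the two follow-ups. Use those visits for maintenance within arms and for comparisons among the three active arms. Label any waitlist comparison there as immediate versus delayed start.
- Reconcile Trial design {8} and Description of the waitlist control group, which give the waitlist APA and education, with Provisions for post-trial care {30}, which names APA only.
- State in the post-trial care section when the APA arm receives the education minutes, so that the APA versus APA + education contrast at follow-up can be interpreted.

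The cost is wording in the protocol and analysis plan, with no extra patients or visits. The trial gives up any claim of benefit over an untreated control beyond 6 months, which the design cannot support anyway.
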